### Primary and secondary endpoints

#### Primary outcome

Symptomatic improvement will be measured by NRS score for average dry mouth (answer to the question – how dry was your mouth on average over the last 24 hours?). A clinically significant response to pilocarpine will be defined as a ≥2 point improvement in xerostomia NRS score compared to placebo. This is in view of previous work, where a 20% (2 cm) improvement or more against the baseline score was considered to be a positive improvement [21,22]. NRS data will be collected on days 2 and 3 of each cycle pair to allow wash-out during day 1.

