(i) Oral health related quality of life will be measured by Oral Health Impact Profile (OHIP) [29], a short 14 item questionnaire that has been validated in a population with xerostomia, although not in cancer or PC.

(a) *Patient Global Impression of Change (PGIC)*:

Is a standardised, validated questionnaire that addresses change in activity limitation, emotions, symptoms and overall quality of life [30].

2. *Timing and content of assessments*

3. *Individual patient reports*

At the end of the trial, the order of medications will be unmasked, and compared with the patient’s observations. Repeated results in the same direction favouring the treatment will be reported in terms of a probability that the observed result is true. The clinical importance of the result will be described by comparing it to a predetermined clinically important change. A clinically significant response to pilocarpine or placebo will be defined as a ≥2 point improvement in xerostomia NRS score compared to baseline, in view of previous work, where a 20% (2 cm) improvement or more against the baseline NRS score was considered to be a positive improvement [21,22]. A report on the patient’s response to pilocarpine will be forwarded to the patient’s doctor so a decision on further treatment can be made.

Palliative care clinicians who recruit participants will most likely also receive the post-treatment report. This potentially may unblind the clinician during the course of the trial in relation to the possible effectiveness of pilocarpine, and particular characteristics of responders. Ideally the clinician recruiting to the study will be a different to the one receiving the results and treating the patient. Collecting data from patients independent of clinicians minimises observer bias.

4. *Withdrawals*

Patients who discontinue the study for whatever reason will be able to resume if their condition can be re-stabilised for at least 1 week. Patients who cannot resume the trial will have their completed cycle results added to the trial dataset for later calculation of the population effect of pilocarpine. If a patient’s withdrawal from the study could be attributed to the intervention, their data will contribute to the analysis under intention to treat principles.

**Table 1 T1:** Schedule of assessments

**Measure**	**Baseline**	**Daily**	**Every 3 days**	**End of 6 day cycle**	**End of trial**
Demographics	x				
Vital Signs	x				
Routine blood test	x				
AKPS	x				x^1^

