### Analysis

#### Sample size calculations

Power calculations were based on the primary outcome variable, the NRS score, and a pooled mean (standard deviation) baseline score across groups of 3.250 (2.975) from Davies et al., 1998 [15] (with correction, 1999). Thomson and Williams’ 2000 [31] article on testing the xerostomia inventory was used to estimate patients’ ICC (intra class correlation). In their table IV, Thomson and Williams give a correlation between standard-question responses that range from 0.20 to 0.76, so we assumed a value of 0.3 (approximately the median). From Bland 2000 [32] [page 204], recognising that r ≈ ICC = *s*_
*b*
_^2^/ (*s*_
*b*
_^2^ + *s*_
*w*
_^2^) where *s*_
*b*
_^2^ is the between subject variance and *s*_
*w*
_^2^ is the within subject variance, we can thus determine that *s*_
*w*
_^2^ ≈ 4.752. Of the 70 palliative care patients randomized by Davies et al. [15], 36 (51%) completed phase I (14 days in length) and 26 (37%) completed phase II (21 days in length after phase I completion). Based on this attrition rate, but recognizing the shorter duration of our study, we expect that approximately 60% of our patients will complete cycle I, 50% will complete cycle II, and 45% will complete cycle III.

If we assume no period effect or treatment × time interaction, then simulations of size N = 10,000 in Stata (Statacorp, College Station, TX) programmed to model the repeated measures design, attrition rates, and *s*_
*b*
_^2^ and *s*_
*w*
_^2^ variances above, then n = 70 patients need to be recruited to detect a 2 cm change in NRS scores between treatments with 80% power at the 5% level of significance. With n = 70, we expect 31 patients will complete all 3 cycles, 4 will complete cycles I and II, 7 will complete cycle I, and 28 will fail to complete any cycles. In contrast, a conventional RCT with similar attrition would require 120 patients.

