#### Data analysis

Data preparation and descriptive reporting will follow that recommended by the CONSORT statement [25].

For each cycle, data from day 1 will be discarded to allow for a wash-out period, and data from days 2 and 3 data will be analysed. All patients with at least one completed treatment cycle will be included in analyses. An effect size will then be calculated between active medication cycles and placebo, thus providing a population measure of effect commensurate with an RCT.

Both individual and population treatment differences will be estimated using hierarchical Bayesian methods and employing noninformative priors using the methods described in Zucker et al. [33], and Schluter and Ware [34]. The likelihood distributions for each model will be assessed for violations and data transformations undertaken, where necessary. Conventional burn-in periods, model convergence and stability diagnostics, and residual checks will be employed [35]. WinBUGS [35] will be used for the Bayesian analysis.

To describe participants’ overall response, three types of Bayesian results will be presented: (i) the mean of the posterior distribution of the mean difference between placebo and stimulant scores, which gives the best estimate of the overall effect size difference between treatments; (ii) the associated 95% credible region, which give intervals of uncertainty (in this case the 2.5 and 97.5 percentile) of the posterior distributions used in (i); and (iii) the posterior probability of the mean difference that stimulant scores were better than placebo scores, which describes the likelihood that the patients will favour the active treatment in future cycles [34]. A patient will be defined to be a ‘responder’ when these estimated values exceed predefined threshold values [34].

Important confounding variables, such as anti-cholinergic load and cause of xerostomia (eg prior radiotherapy), will in included in adjusted analyses and report treatment effects (or success differences) over the various variable stratifications and combinations, following the method advocated by Zucker and colleagues [33].

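### The posterior probability that the mean difference favours pilocarpine is described as the chance that patients will favour it in future cycles; these are different quantities, and the second is clearly lower when the mean effect is positive

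*Protocol article*

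**What the plan says.** The Data analysis section plans "hierarchical Bayesian methods and employing noninformative priors" for individual and population treatment differences. To describe participants' overall response, "three types of Bayesian results will be presented": the posterior mean of the mean difference, its 95% credible region, and, as item (iii), "the posterior probability of the mean difference that stimulant scores were better than placebo scores". I read stimulant here as pilocarpine. The sentence then says what item (iii) means: "which describes the likelihood that the patients will favour the active treatment in future cycles". The same paragraph classifies a patient as a responder "when these estimated values exceed predefined threshold values".

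Two other places bear on how far the point reaches. The Primary outcome section sets the clinical yardstick: "A clinically significant response to pilocarpine will be defined as a ≥2 point improvement in xerostomia NRS score compared to placebo". Under Patient assessment, the paragraph on individual patient reports says "Repeated results in the same direction favouring the treatment will be reported in terms of a probability that the observed result is true", and adds that clinical importance will be judged against a predetermined change. The article defines no posterior predictive quantity.

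**The concern.** Item (iii) answers one question: given the data, how sure are we that the average difference lies on the pilocarpine side of zero? The interpretation answers another: how likely is it that patients will do better on pilocarpine in cycles still to come? The second depends on how much a cycle difference varies around a patient's own mean and, for patients outside the trial, on how much true effects vary between patients. Collecting more data shrinks neither source of variation.

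For any positive average effect, however small, item (iii) therefore tends to 1 as cycles and patients accrue, while the chance that a future cycle favours pilocarpine settles at a value below 1. A trial report following the plan's wording would present near-certainty about the average as near-certainty of benefit in future use. The N-of-1 trials section makes variation in individual response a condition of the design, so the interpretation omits the very feature that the design was chosen to study.

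**Working it through.** The article gives no numerical value for item (iii), so there is none to reproduce. The check compares the two probabilities under the plan's own design inputs.

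**Inputs from the Sample size calculations section**
- Within-subject variance s_w² = 4.752, as stated. As a sensitivity value, the stated SD of 2.975 and ICC of 0.3 give 0.7 × 2.975² = 6.195.
- Expected completers: 31 with three cycles, 4 with two, 7 with one. Cycles: 31×3 + 4×2 + 7×1 = 108.
- Design effect: the trial is sized "to detect a 2 cm change in NRS scores between treatments with 80% power at the 5% level of significance".

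**Assumptions (mine)**
- Flat prior on the mean, normal model, variances treated as known.
- One score per period. As an alternative, days 2 and 3 averaged as if independent, which halves the variance.
- Between-patient SD of the true effect, τ: the article expects variation but gives no size, so τ = 0 in the main case, with 1 and 2 points as the range.

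**Formulas**, with d the estimated mean difference (positive favours pilocarpine) and v = 2·s_w² the variance of one cycle difference:
- Item (iii): Φ(d / SE). With τ = 0, SE = √(v/108). With τ > 0, SE = [Σ 1/(τ² + v/nᵢ)]^(−1/2) over the 42 patients, where nᵢ is the number of cycles completed.
- Chance that a future cycle favours pilocarpine: Φ(d / √(SE² + τ² + v)). With τ > 0 this is for a new patient.

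**Main case** (s_w² = 4.752, one score per period, τ = 0)
- v = 9.504; SD of one cycle difference = √9.504 = 3.08; SE = √(9.504/108) = 0.297.
- d = 2: item (iii) = Φ(2/0.297) = 1.000; future cycle = Φ(2/√(9.504 + 0.088)) = Φ(0.646) = 0.74.
- d = 1: 1.000 (0.9996) against 0.63.
- d = 0.5: 0.954 against 0.564.

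**Range** over s_w² of 4.752 or 6.195, one score or two days averaged, and τ of 0, 1 or 2:

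| Mean difference | Item (iii) | Future cycle favours pilocarpine | Gap, points |
|---|---|---|---|
| 2 | 1.000 | 0.69 to 0.82 | 18 to 31 |
| 1 | 0.984 to 1.000 | 0.60 to 0.68 | 32 to 39 |
| 0.5 | 0.86 to 0.99 | 0.55 to 0.59 | 31 to 40 |

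The gap must close again as the effect approaches zero, because both probabilities then go to 0.5.

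**Between-patient variation.** With d = 1, τ = 2, s_w² = 4.752 and one score per period, SE = 0.434. Item (iii) is 0.989. The probability that a new patient's true mean favours pilocarpine is Φ(1/√(0.434² + 2²)) = 0.69, and for one future cycle in that patient it is 0.61.

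**Accrual.** With d = 0.5 in the main case, four times the data (432 cycles) would move item (iii) from 0.954 to 0.9996. The future-cycle probability would stay at 0.564.

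**One patient analysed alone**, three cycles, observed difference 2, s_w² = 4.752, one score per period: posterior probability Φ(2/√(9.504/3)) = 0.87; predictive probability for that patient's next cycle Φ(2/√(9.504 + 9.504/3)) = 0.71. Across observed differences of 1 to 3 and the same choices of variance and scores per period, the gap is about 9 to 16 points.

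**The case against.** The best defence is that the quantity itself is correctly defined and only the explanatory clause is loose. The clause speaks of patients in the plural, inside a sentence about overall response, and can be read as meaning patients on average. It also cites a methods paper that is not at hand. On this view the model, data set and decision rule are unaffected. Most of that is fair: the remedy is mainly wording. But the clause is the stated meaning of one of three headline results, and it refers to future cycles. A reader taking it at its word would be misinformed, and a citation does not make the two quantities equal.

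The defence is right against several stronger readings that a reader might infer:
- *The paragraph on individual reports makes the same error.* It does not. Its phrase about the probability that a result is true is loose, but it says nothing about future cycles and does not cite item (iii).
- *Clinical importance is ignored because item (iii) is measured against zero.* The article reports the effect size and its interval alongside, and compares individual results with a clinically important change.
- *The true prospect of benefit is near a coin toss.* That holds only for a small assumed effect. At the 2-point design effect the predictive figure is about 0.74.
- *Individual reports will show near-certainty.* The near-certain figures come from 108 pooled cycles. A patient's own three cycles give a smaller gap.
- *Three favourable cycles out of three arise by chance in (1/2)³ = 12.5% of patients with no drug effect.* This is true, but it does not measure the difference between a posterior and a predictive probability.

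**Conclusion.** The point holds as a misinterpretation of the population summary. Item (iii) is the probability that the average effect favours pilocarpine, and the article wrongly presents it as the likelihood that patients will favour the drug in future cycles. At the design effect the stated result would be 1.000, while the quantity described is about 0.74 (0.69 to 0.82). The gap is generally wider at mean differences of 0.5 to 1 point. It is smaller, though still present, for a single patient's three-cycle posterior.

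The exact figures rest on the flat prior, the normal model, the treatment of days 2 and 3, and the assumed τ. The direction held in every combination run with a positive mean effect. If the mean favoured placebo, item (iii) would understate the chance rather than overstate it. The documents do not show that the planned model, the effect estimate or its credible region is wrong.

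**What to change.** In the Data analysis section, describe item (iii) as the posterior probability that the average effect favours pilocarpine, and remove the clause about future cycles. If statements about future cycles or patients are wanted, report from the same WinBUGS model the posterior predictive probability that a new cycle favours pilocarpine, once for the same patient and once for a new patient, labelled separately from item (iii). The posterior probability that the difference is at least 2 points would be a useful optional addition.

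The cost is a wording change and a few extra monitored nodes. Design, sample size and data collection stay as they are. The drawback is that the predictive figures will look less favourable than item (iii), and the report will need a sentence explaining why the two differ.

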## Discussion

Xerostomia is a very frequent and distressing symptom in PC patients with significant physical, social and psychological consequences which compromise the quality of life of patients. Managing dry mouth with treatment supported by the best possible evidence will improve the functional status of patients, and improve quality of life (QOL) for patients and carers. The research question is one of the most important ones in PC. Trial findings will provide evidence to service providers, policy makers and consumers to develop policies and practice around the use of pilocarpine for dry mouth in PC patients.

It is important to assess n-of-1 trial methodology in a range of medications and symptoms and in an array of PC situations. Using n-of-1 trials will help to accelerate the rate of accumulation of high-grade evidence to support clinical therapies used in PC. The method will augment the evidence base for PC clinical therapies, contribute to lessening the uncertainty that surrounds many therapies in advanced cancer, and minimize side effects from treatments without proven benefit. This trial thus forms an important and significant part of the world’s first systematic evaluation of n-of-1 trials in PC.

Moreover, if n-of-1 trial methodology proves to be robust, it will be suitable for many other areas of clinical PC as an alternative method of gathering evidence of similar strength to RCTs, but requiring far fewer subjects to be recruited. N-of-1 trials will accelerate development of the PC evidence base to improve care offered to this very disadvantaged and frail group and make a significant contribution to quality of life for people with terminal illness and their carers.

## Abbreviations

AR: Adverse (drug) reaction; AE: Adverse event; AKPS: Australian karnofsky performance scale; ALT: Alanine aminotransferase; AST: Aspartate aminotransferase; CRF: Case report form; DAP: Data analysis plan; DSMC: Data safety monitoring committee; EORTC-QLQC15-PAL: European Organisation for Research and Treatment of Cancer (EORTC) Quality of Life Group shortened the QLQ-C30 specifically for use in palliative care to a 15-item version entitled the EORTC QLQ-C15-PAL; GCP: Good clinical practice; ICC: Intra-class correlation; IRB: Institutional review board; MPH: Methylphenidate; NCI: National cancer institute; n-of-1: Single patient trials; NRS: Numerical rating scale; OHIP: Oral health impact profile; PaCCSC: Palliative care clinical studies collaborative; PC: Palliative care; QOL: Quality of life; RCT: Randomised controlled trial; SAE: Serious adverse event; SAR: Serious adverse (drug) reaction; SPT: Single patient trials; SUSAR: Suspected unexpected serious adverse reaction; TABS: Tablets; UQ: The University of Queensland; VAS: Visual analogue scale; WHO: World Health Organisation; XI: Xerostomia inventory; XQ: Xerostomia questionnaire.
